### 2.5. Physician Randomization

#### 2.5.1. Sequence Generation

We will use block randomization [43] to assign the ExRx delivery sequence among physicians (N = 24), stratified by those who meet the PA guidelines [44] (n = 12) and those who do not meet them (n = 12). Within each PA level, physicians will be randomly assigned to one of two delivery sequences using permuted blocks of four: (1) P3-EX followed by PAVS, or (2) PAVS followed by P3-EX. This approach aims to ensure equal allocation of the ExRx delivery sequences across PA levels to control for the potential confounding effect of physician PA levels on the primary aim of the study [45].

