### 2.13. Sample Size Estimation

We conducted a power analysis using G*Power (version 3.1.9.6, Heinrich Heine University Düsseldorf, Düsseldorf, Germany) [68] to obtain a conservative usability rating of P3-EX to evaluate the primary aim of the study. We obtained the lowest observable usability score of 4.650 ± 0.759 (mean ± SD) converted from our feasibility survey study pilot data [32] to compare to the null hypothesis middle score of 4.0 on the mHealth Application Usability Questionnaire [50]. Using a one-sided Wilcoxon signed-rank (one sample case) test [69] at the significance level (α) of 0.01 and calculated effect size between the observed and middle score of Cohen’s d = 0.856, we determined that 19 physicians are required to achieve 85% power. Therefore, we will use 19 physicians to achieve 85% power (α of 0.01), and recruit two patients per physician to complete 38 patients. Using an observed attrition of 20% for patients in the study [70,71,72,73], this trial will aim to recruit 24 physicians and 48 patients (24 patients per group). Because physicians’ PA levels could influence how they perceive and rate the delivery of an ExRx [45], we aim to recruit half of the physicians who meet PA guidelines (n = 12) [44] and half who do not (n = 12).

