#### 2.14.1. Evaluation of the Primary Aim

We will use the following statistical approaches to evaluate the feasibility and acceptability of P3-EX for physicians to use to prescribe exercise to patients with CVD risk factors. We will use a one-sided Wilcoxon signed-rank (one sample case) test [69] to assess whether the physician mHealth Application Usability Questionnaire ratings of P3-EX and the PAVS are above the null hypothesis middle score of 4.0 on the Likert scale [50], and whether System Usability Scale ratings are above the average score of 68/100 [78]. We will use a linear mixed effects model adjusting for the delivery order of P3-EX and PAVS and the time between delivery as potential covariates and interactions between these two covariates to assess differences in the physician usability questionnaire scores between P3-EX and the PAVS. We will use normal linear regression to determine the strength of relationships between the three domains on the mHealth Application Usability Questionnaire and usage time of P3-EX and PAVS.

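### The physician mixed model omits physician physical-activity level, the factor that stratifies recruitment and randomisation; this causes no bias, but including it is nearly free

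*Protocol article*

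**What the plan says.** Section 2.13 of the protocol article sets a quota of 12 physicians who meet the PA guidelines and 12 who do not. The reason given is that physicians' "PA levels could influence how they perceive and rate the delivery of an ExRx". Section 2.5.1 stratifies the randomisation of delivery sequence by the same factor, in permuted blocks of four, "to control for the potential confounding effect of physician PA levels on the primary aim of the study". The means it names is equal allocation of the two sequences across PA levels.

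Section 2.14.1 lists three analyses of the primary aim:
- one-sample Wilcoxon tests of the physician ratings, against 4.0 for the mHealth questionnaire and 68 for the System Usability Scale;
- a linear mixed model comparing P3-EX with PAVS, "adjusting for the delivery order of P3-EX and PAVS and the time between delivery as potential covariates", with the interaction of those two;
- linear regressions relating questionnaire domains to usage time.

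None of them names physician PA.

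**The concern.** A factor thought important enough to fix recruitment and to stratify randomisation would normally appear in the model that compares the methods. Section 2.14.1 is not merely silent: it lists the model's covariates, and the stratification factor is not among them. For period and carryover effects, section 4.2 relies both on randomising the sequence and on adjusting in the analysis. PA gets only the design half.

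Two things are at stake. One is precision, since variation between PA strata stays in the error term although the design fixes the mix of strata. The other is that no listed analysis would show whether the P3-EX v PAVS difference depends on the physician's own activity. In addition, balancing the order of the two methods cannot act on the powered question, which is whether the P3-EX rating exceeds 4.0.

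**Working it through.** **1. The plan's own sample size (section 2.13).** Inputs: mean 4.650, SD 0.759, null 4.0, one-sided α 0.01, 85% power, 20% attrition.
- d = (4.650 − 4.0)/0.759 = 0.856, as stated.
- Power at N = 19 is 84.7% for the Wilcoxon test by the asymptotic-relative-efficiency method (effective n = 19 × 3/π, normal parent), 84.1% by simulating the exact test and 86.8% for a t-test. The stated 19 and 85% reproduce within tolerance.
- 19/0.8 = 23.75, so 24 physicians.

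This sizing uses the unadjusted SD, so nothing below changes it.

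**2. Is sequence balanced over PA?** Twelve per stratum is three full blocks of four, which gives 6:6 in each stratum. The design delivers this exactly if both quotas fill.

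**3. P3-EX v PAVS contrast.** Let physician i have level u_i, which includes any PA main effect. The within-physician difference D_i = (P3-EX rating) − (PAVS rating) does not contain u_i, so a PA main effect cancels. This assumes that the mixed model has a physician effect. Only a method-by-PA interaction γ survives. With a 12/12 mix it adds about γ²/4 to the variance of D_i if PA is left out.

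A simulated 24-physician crossover (3,000 runs per setting, blocks of four in each stratum) checks this. Its assumptions are a between-physician SD of 0.6, a residual SD of 0.46 per rating, a period effect of 0.3, a true method difference of 0, and PA main effects of 0, 0.5 and 1.0. The size of the PA main effect made no difference to any result.

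| Physicians | Interaction γ | Model SE without PA | Model SE with PA |
|---|---|---|---|
| 24 | 0 | 0.131 | 0.131 |
| 24 | 0.5 | 0.141 | 0.131 |
| 19 (random loss) | 0 | 0.148 | 0.148 |
| 19 (random loss) | 0.5 | 0.159 | 0.148 |

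The mean estimate was within 0.003 of zero in every setting. With 24 physicians its empirical SD was 0.129 with and without PA. With γ = 0.5 the unadjusted SE is therefore too large by 0.141/0.131 = 1.08, about 8%. That error is conservative.

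**4. One-sample P3-EX mean.** Sequence balance has no role here; only the 12/12 quota acts, by fixing the PA mix. Take 0.759 as the SD of a 50:50 mix, and let Δ be the difference between strata in the mean P3-EX rating. The within-stratum SD is √(0.759² − Δ²/4).

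| Assumed Δ | Within-stratum SD | Ratio to 0.759 | SE smaller by |
|---|---|---|---|
| 0.25 | 0.749 | 0.986 | 1.4% |
| 0.5 | 0.717 | 0.944 | 5.6% |
| 1.0 | 0.571 | 0.752 | 25% |

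**5. If dropout is uneven.** Suppose the planned fall from 24 to 19 came entirely from one stratum (12/7, the worst case). The raw P3-EX mean would move by (12/19 − 0.5) × Δ = 0.132 × Δ. That is about 0.07 points for Δ = 0.5 and 0.13 for Δ = 1.0, against the expected margin of 0.65 over 4.0. A 50:50-weighted mean restores the designed mix.

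**The case against.** The strongest defence is that section 2.5.1 promises control by design and nothing more, and that full blocks deliver it. Section 4.2 adds that the crossover itself reduces variation in ratings due to PA. A one-sample test has no comparison to confound, and its PA mix is set by the quota. All of this stands. A reader might infer from the omission that the intended control fails, or that the primary results are confounded by PA. The documents do not support that: the stated control is sequence balance, a PA main effect drops out of the within-physician contrast, and the simulation shows no bias.

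It also stands that no document gives a PA difference in ratings. A Δ of 0.5 is 0.66 SD and a Δ of 1.0 is 1.3 SD, so the 25% figure belongs to a very large effect. The PA mix behind the pilot SD is not stated either. Section 1.2 sets no aim about effect modification. The SE of the interaction would be about twice that of the contrast (2 × 0.131 = 0.26), so only an interaction of roughly 0.7 points (2.8 × 0.26) would be detectable with 80% power. A second, model-based decision against 4.0 would compete with the Wilcoxon test and lean on normality.

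The appeal to the analysis plan carries less weight. That plan is not shown and may include PA, but the article itself lists the model's covariates without the factor it randomises by.

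**Conclusion.** The point holds as a modest one about efficiency and coherence. The stated physician mixed model omits the stratification factor. The contrast stays unbiased, the sample size is unaffected, and false positives are not inflated. The cost is a conservative SE for the contrast if method and PA interact, about 8% for an assumed 0.5 points and none without an interaction. For the P3-EX mean, the forgone gain ranges from about 1% to 25% of the SE over assumed PA differences of 0.25 to 1.0 points. These sizes rest on assumed variance components and PA effects, on a physician effect in the mixed model, and on reading 0.759 as the SD of an even PA mix.

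**What to change.** In section 2.14.1, add PA stratum and a method-by-PA-stratum term to the physician mixed model. Code the stratum as ±½, so that the method effect is the 50:50 average over strata. From the same model, report the P3-EX mean with its interval, weighted 50:50 over strata, as a supportive and descriptive estimate. Keep the Wilcoxon test as the only decision rule against 4.0, and label any per-stratum means exploratory. If the investigators prefer not to adjust, one sentence saying that PA is controlled by design only would remove the mismatch.

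Physician PA is already collected at the orientation visit (section 2.4). The cost is one or two degrees of freedom among about 19 to 24 physicians, with no change to sample size or conduct. If the analysis plan already contains these terms, only the article's covariate list needs to be aligned with it.

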#### 2.5.2. Allocation Concealment and Implementation

[name], who is not involved in data collection or outcome assessment to maintain allocation concealment, will create a computer-generated randomization schedule (https://www.sealedenvelope.com/, 30 November 2025) [46] maintained on a university-owned desktop computer with password protection. [name] will prepare sequentially numbered, sealed envelopes in advance, and will only open them after physicians and patients are enrolled. [name] will inform physicians of their random assignment via email after their first patient is enrolled.

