### 2.1. Trial Design

The P3-EX Feasibility Trial is a feasibility and pilot efficacy RCT with a two-arm crossover exploratory design (Figure 1). Physicians (N = 24) will be individually randomized with a 1:1 allocation ratio to deliver P3-EX to one of their patients (n = 24) and PAVS to another patient (n = 24) in random sequence. Because physicians will deliver P3-EX and PAVS to patients during their routine healthcare appointments that are scheduled in advance of their enrollment, we will not implement a washout period for physicians between their delivery of P3-EX and PAVS, but will control for potential period or carryover effects in statistical analyses.

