### 2.4. Physician and Patient Recruitment and Enrollment

[name], [name], and [name] will email their physician colleagues, and physicians will be notified using listservs and newsletters distributed by Hartford HealthCare, UConn Storrs, and UConn Health. Flyers and leaflets will be used at the hospital clinics and community locations. Physicians will complete an online screener and attend a one-on-one virtual study orientation visit led by [name] and an RA over Microsoft Teams to provide consent; confirm eligibility; provide demographics including age, gender, ethnicity, medical specialty, the number of years in practice, prior experience using digital health tools; assess barriers to and confidence with ExRx and PA levels; be orientated to the study procedures; and receive brief ExRx delivery training regarding their patients. [name] will use a standardized script from our laboratory to verbally and uniformly train physicians on the study procedures to deliver the P3-EX and PAVS ExRxs, detailed in their ExRx Instruction Manual (Supplementary File S2), and physicians will not practice using P3-EX or PAVS prior to using each ExRx method.

The enrolled physicians will identify patients who have upcoming appointments with them through the hospitals’ scheduling or electronic medical record systems. Physicians will briefly screen health history profiles of their upcoming patients using the study inclusion criteria. Physicians will inform patient candidates by uploading an electronic flyer to their MyChart account and by phone call. Patients will complete a phone screening and attend two one-on-one in-person study visits led by [name] and an RA to provide consent; confirm eligibility; provide demographics including age, sex, gender, ethnicity, education level, household composition, salary, and technology use; and undergo pre-intervention assessments of PA levels and CVD risk factors.

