#### 2.5.3. Blinding

[name], who will conduct physician and patient enrollment and pre- and post-intervention outcome assessments, will not have access to the random allocation sequence. [name] will be blinded to group assignments during patient pre-intervention outcome assessments, and laboratory technicians will be blinded when assessing all blood lipid-lipoprotein and glucose values. Patients will disclose details of their healthcare appointment to [name] after completing all pre-intervention outcome assessments.

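### A physician can know the second patient's arm before choosing that patient (up to 24 of 48 patients), and the assessor may be able to deduce it before that patient's baseline

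*Protocol article*

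**What the plan says.** All references are to the Protocol article.

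- **What is randomised.** Section 2.5.1: "physicians will be randomly assigned to one of two delivery sequences using permuted blocks of four", the two orders being P3-EX first or PAVS first. Section 2.1 has each physician "to deliver P3-EX to one of their patients (n = 24) and PAVS to another patient (n = 24) in random sequence".
- **When the envelope is opened.** Section 2.5.2, on the person who prepares the envelopes: "will only open them after physicians and patients are enrolled".
- **When the physician is told.** The next sentence of Section 2.5.2: a team member "will inform physicians of their random assignment via email after their first patient is enrolled".
- **Who finds the patients.** Section 2.4: "The enrolled physicians will identify patients who have upcoming appointments with them". The physicians also check health histories against the inclusion criteria and make the first approach. Phone screening, consent and confirmation of eligibility follow.
- **Blinding.** Section 2.5.3 says that the person who enrols and measures patients has no access to the sequence and "will be blinded to group assignments during patient pre-intervention outcome assessments". It then says "Patients will disclose details of their healthcare appointment" once the pre-intervention assessments are done. Laboratory technicians are blinded for lipids and glucose.

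**The concern.** Allocation concealment is meant to stop whoever recruits a patient from knowing which arm that patient will enter. Here the recruiter is the physician, and one disclosure settles two allocations. If it comes between the two recruitments, the second patient can be selected, even unconsciously, for motivation, severity or number of risk factors to suit a known arm. Randomising the order of delivery does not undo that.

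The baseline has a similar gap. The assessor is kept from the sequence, but the timing of each patient's disclosure depends only on that patient's own baseline. Nothing links it to the other patient of the same physician.

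What is exposed is the patient comparison of P3-EX with PAVS under the secondary aim (Section 2.14.2). Section 5 intends those data to power a larger trial, so a bias could carry forward. The primary one-sample test of physician usability is touched only indirectly, through which patient the physician picks for P3-EX.

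**Working it through.** **Step 1. The plan's own counts.** Section 2.13 needs 19 physicians and 38 patients and allows 20% attrition. 19 / 0.8 = 23.75, rounded up to 24. 38 / 0.8 = 47.5, rounded up to 48. Both targets reproduce. The point depends on these counts and not on the power calculation.

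**Step 2. Does the sequence determine the second arm?** There are two sequences, each using each method once. If the first patient gets P3-EX, the second gets PAVS with certainty, and the reverse. Even without the email, delivering the first prescription would tell the physician the second arm. Concealment of the second patient therefore depends on that patient being named before disclosure.

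**Step 3. The two sentences of Section 2.5.2 side by side.** The envelope must be opened before the assignment can be emailed.
- If the envelope sentence means both of a physician's patients, an email triggered by the first enrolment comes too early, and the sentences conflict.
- If it means only the first patient, they agree, but the second patient's allocation is not concealed from the recruiter.

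Either way the text does not assure concealment for the second patient.

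**Step 4. How many patients?** There is one second patient per physician: 24 of 48, or 50%. With 12 physicians per stratum and blocks of four (12 / 4 = 3 full blocks), sequences balance 12 to 12, so 12 second patients fall in each arm. This is a maximum. If a share f of physicians identify their second patient after the email, 24f are exposed:

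| f | Exposed | Share of 48 |
|---|---|---|
| 0.25 | 6 | 12.5% |
| 0.50 | 12 | 25% |
| 0.75 | 18 | 37.5% |
| 1.00 | 24 | 50% |

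**Step 5. The assessor.** Deduction needs the first patient's appointment and disclosure to come before the second patient's baseline. No section fixes that order. Section 2.14.1 uses time between deliveries as a covariate, so a varying gap is foreseen.

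**Step 6. Illustrative size.** The documents give no figure for selection. Assume that second patients differ between arms by s SD, that first patients do not differ, and that all second patients are affected. The whole-sample shift is s/2. With 24 per arm the standard error is sqrt(2/24) = 0.289 SD. The noncentrality is (s/2) / 0.289, for an unadjusted two-sided t-test at 0.05 with 46 degrees of freedom:

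| s (assumed) | Whole-sample shift | Noncentrality | False-positive rate |
|---|---|---|---|
| 0.10 | 0.05 | 0.17 | 5.3% |
| 0.25 | 0.125 | 0.43 | 7.1% |
| 0.50 | 0.25 | 0.87 | 13.6% |
| 0.75 | 0.375 | 1.30 | 24.6% |
| 1.00 | 0.50 | 1.73 | 39.6% |

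With partial exposure the shift is f × s/2. For example, f = 0.5 with s = 0.5 gives 0.125 SD and so 7.1%. At 19 per arm the rates for s = 0.25 and 0.50 are 6.6% and 11.7%.

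**The case against.** A reader might infer that half of the patient sample has no allocation concealment and no baseline blinding. The documents do not support that, for these reasons:

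- **Order of events.** No section says that the second patient is always chosen after the email. Section 2.1 has appointments scheduled before enrolment, so both patients may already be identified. The envelope sentence can be read as waiting for both, and an email sent after the second enrolment is also, literally, after the first.
- **Assessor.** Loss of baseline blinding is a possible deduction, not a stated event. Names are masked, so it is probable but not certain that the person who hears about the appointment is the one who measures. Section 4.3 makes it likely, since the person running guidance visits also takes post-intervention measures and knows the arms by then.
- **Measures.** Lipids and glucose stay blinded. Blood pressure uses automatic monitors with an agreement rule, and activity is recorded by device or by the patient. This limits what an unblinded assessor could change.
- **Safeguards.** The physician is not described as the one who confirms eligibility, and Section 2.14.2 allows adjustment for demographics, medication and pre-intervention values.
- **Role of the comparison.** It is exploratory. The primary question is physician usability, and the physician's sequence and the first patient's allocation are concealed as written.

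All of this stands and limits the point. It does not remove it: nothing in the text requires the second patient to be named before disclosure, and covariate adjustment cannot remove selection on motivation that is not measured.

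**Conclusion.** The point holds in a conditional form. As written, Section 2.5.2 does not assure concealment for a second patient identified after the physician is told the sequence, and Section 2.5.3 does not protect the assessor's baseline blinding for that patient. The two sentences of Section 2.5.2 need reconciling in any case.

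Exposure is at most 24 of 48 patients, and fewer if some second patients are identified earlier. It falls mainly on the exploratory patient comparison. The false-positive rate of about 7% to 14% rests on an assumed between-arm shift of 0.25 to 0.5 SD in second patients, all of them affected, and on an unadjusted test. It is an illustration, not an estimate from the documents. That physicians can learn the second arm early is clear from the text; how often it would matter is not.

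**What to change.** Rewrite the two sentences of Section 2.5.2 as one rule: the envelope is opened and the physician emailed only after both of that physician's patients have been named and pre-screened and, where appointment dates allow, have consented and completed all pre-intervention assessments.

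Where full pairing is not possible:

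1. Where feasible, keep the first patient's appointment details from the assessor until the second patient's baseline is complete. Naming the second patient early does not by itself protect the assessor's blinding.
2. Record for each pair whether the second patient was enrolled before disclosure. Count a replacement for a named patient who declines as enrolled after it.
3. Add a sensitivity analysis of the patient comparison limited to pairs enrolled before disclosure. It will be imprecise: with 12 such pairs the standard error is sqrt(2/12) = 0.41 SD, against 0.29 SD for all 24.

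Sample size is unchanged. The cost is scheduling: some first patients may wait until their partner is named. Completing both baselines before the first routine appointment means two in-person visits, fasting blood tests and accelerometer wear for each patient, which pre-scheduled appointments will not always permit. That is why full pairing is asked for only where dates allow.

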#### 2.5.3. Blinding

[name], who will conduct physician and patient enrollment and pre- and post-intervention outcome assessments, will not have access to the random allocation sequence. [name] will be blinded to group assignments during patient pre-intervention outcome assessments, and laboratory technicians will be blinded when assessing all blood lipid-lipoprotein and glucose values. Patients will disclose details of their healthcare appointment to [name] after completing all pre-intervention outcome assessments.

